### Statistical analysis

All analyses are to be based on the initial treatment assignment (intention to treat). Missing data will be replaced with multiple imputation to primary and secondary outcome variables. Differences between the groups at 3 and 6 months and within-group changes are to be compared using the paired *t* test. All statistical analyses will be performed using IBM Statistical Package for the Social Sciences (SPSS) Statistics version 17.0 software. A significance level of 0.05 is used for each test.

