Previous research has shown that, in many cases, prosthodontic rehabilitation alone, such as complete dentures [1, 6–8], implant overdentures [2, 4, 9–11], and other prosthetic treatments [12–14], for older patients in the absence of tailored dietary counseling is inadequate to attain a significant improvement in nutritional status. Most researchers suggest that dietary counseling is necessary. There has been little research investigating the impact of providing dietary counseling to edentulous individuals wearing complete dentures [1, 3, 15–17]. In a randomized controlled study [16] aimed at edentulous individuals without problems with their current complete dentures or mandibular implant overdentures, tailored dietary counseling benefited both complete dentures wearers and mandibular implant overdenture wearers. Mandibular implant overdenture wearers showed moderately greater dietary improvements when compared with patients wearing conventional dentures. In another randomized controlled study [1] aimed at edentulous individuals who request new dentures, simultaneous tailored dietary counseling delivered by a nutritionist on two occasions and provision of new complete dentures in combination improved fruit and vegetable intake. On the other hand, a combination of use of a denture adhesive and simple dietary advice in the form of government-issued dietary pamphlets issued by dentists produced significant improvement in dietary intake among edentulous individuals wearing current complete dentures for more than one year; there was especially an improvement in the number of portions of fruit and vegetables [3].

There has been no research investigating whether simple dietary advice in pamphlet form combined with provision of new complete dentures improves dietary intake among edentulous individuals who request new dentures. Therefore, we plan to test the null hypothesis that there would be no difference in dietary intake between edentulous individuals provided with simple dietary advice and new complete dentures and edentulous individuals provided with new dentures alone.

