## Methods/design

This double-blind, parallel, randomized controlled trial is investigating the effect of a combination of simple dietary advice and provision of new complete dentures on dietary intake in elderly edentulous individuals. The study follows the 2010 Consolidated Standards of Reporting Trials (CONSORT) statement [18]. The study protocol and informed consent documents have been approved by the institutional ethics committee at Tokyo Medical and Dental University (TMDU, registry number 1144). The trial is registered with the University Hospital Medical Information Network (UMIN) Center (UMIN-CTR Clinical Trial, Unique Trial Number: UMIN000017879).

All participants are required to give written informed consent. The study participants are to be randomly allocated either to the dietary intervention group or to the control group. All participants receive complete denture treatments.

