#### Primary outcome measures

The primary outcome measures are fruit, vegetable, and protein intake measured using a brief-type self-administered diet history questionnaire (BDHQ). The BDHQ enquires about the frequency of intake of 75 food items during the previous month. The daily intake of approximately 30 nutrients and about 50 food items is estimated. The validity and reliability of the BDHQ are established [24, 25].

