### Sample size estimation

The sample size was determined based on the two primary outcomes: changes in the weight of fruit and vegetable intakes and in the weight of protein intake. In case of change in the weight of fruit and vegetable intakes, 29 individuals per group would provide 80 % power to detect a difference of 125 g per day in intake, with a two-sided test at a 0.05 level of significance for the primary outcome. In case of change in the weight of protein intake, 30 individuals per group would provide 80 % power to detect a difference of 15 g per day in protein intake, with a two-sided test at a 0.05 level of significance for the primary outcome. We also anticipated a 15 % rate of loss to follow-up. Accordingly, we adjusted our target baseline sample size to 35 per group.

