### Randomization and allocation

Eligible study participants are to be randomly assigned to the dietary intervention group or the control group in an alternate fashion. The randomization sequence has been established with block sizes of 10 and an allocation ratio of 1:1 before recruitment commences and is to be concealed in opaque consecutively numbered envelopes. After the decision on participants’ enrollment, the envelopes will be opened. Patient enrollment and randomization will be undertaken by two outcome assessors (HS and NA). Participants and clinicians will be blinded to the group allocation of each participant. The participants will be given repeated instructions not to reveal their group allocation to clinicians. Any questions from participants during the intervention period will be answered by the outcome assessors (AJ, HS, and NA).

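### The only test named for the between-group comparison is a paired t test, but the two arms are independent and unmatched, so the test of the primary hypothesis is mis-specified

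*Protocol article*

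**What the plan says.** The Statistical analysis section of the protocol article gives one test for two kinds of comparison: "Differences between the groups at 3 and 6 months and within-group changes are to be compared using the paired *t* test". The abstract carries the same sentence. No independent-samples test, ANCOVA or mixed model is named anywhere in the article.

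The design is described as follows.

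- Methods/design: "This double-blind, parallel, randomized controlled trial is investigating the effect of a combination of simple dietary advice and provision of new complete dentures". Each person belongs to one arm: "The study participants are to be randomly allocated either to the dietary intervention group or to the control group".
- Randomization and allocation: "The randomization sequence has been established with block sizes of 10 and an allocation ratio of 1:1". No matching factor is described.
- Background: the null hypothesis concerns the contrast between arms. It reads, in part: "there would be no difference in dietary intake between edentulous individuals provided with simple dietary advice and new complete dentures and edentulous individuals provided with". The comparison group there is the one without the advice.
- Sample size estimation: the figures are per group, for a difference in change. For fruit and vegetables, "29 individuals per group would provide 80 % power to detect a difference of 125 g per day in intake"; for protein, "30 individuals per group would provide 80 % power to detect a difference of 15 g per day in protein intake". After allowing for 15% loss the target is 35 per group.

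**The concern.** A paired t test works on differences within linked pairs. Baseline and follow-up on one person form such a pair, so the test suits within-group change. Between the arms of this trial there is no such link. Applied literally, the sentence makes the analyst join each intervention participant to some control participant by a rule that the protocol does not give, and the result then depends on that rule.

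This is the only test stated for the primary hypothesis. It is a positive statement of the wrong test, not a detail left to a fuller document. If it is put right only after the results are known, the choice of the primary test becomes post hoc.

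**Working it through.** **1. The plan's own figures.** No SD is given, so 29 and 30 per group cannot be reproduced forwards. Solved backwards for two independent groups (two-sided 0.05, 80% power), they imply an SD of about 167 to 170 g/day for fruit and vegetables and 20.4 to 20.7 g/day for protein. At 30 per group the standardised difference with 80% power is 0.736. For loss to follow-up, 30 × 1.15 = 34.5, rounded up to 35, while 30 / 0.85 = 35.3, rounded up to 36. The stated 35 leaves 35 × 0.85 = 29.75. The sample size is therefore not in question here.

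**2. Why row order matters.** Take two arms of equal size n and equal SD, and let r be the sample correlation created by whatever pairing is used. The mean difference is the same under every pairing. Only the standard error and the degrees of freedom change:

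- unpaired: t on 2n − 2 = 58 df for n = 30
- paired: t / √(1 − r) on n − 1 = 29 df

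Under random pairing r varies around 0 with SD of about 1/√(n − 1) = 1/√29 = 0.186, so its central 95% range is about ±0.364. For an unpaired p of 0.05, t = 2.002:

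- r = +0.364: t = 2.002/√0.636 = 2.51, paired p = 0.018
- r = 0: t = 2.002, paired p = 0.055
- r = −0.364: t = 2.002/√1.364 = 1.71, paired p = 0.097

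**3. Simulated re-pairing** (normal data, 20,000 pairings per data set) agrees:

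| Per arm | Unpaired p | Central 95% of paired p | Pairings with p < 0.05 |
|---|---|---|---|
| 30 | 0.03 | 0.010 to 0.067 | 83% (17% lose significance) |
| 30 | 0.05 | 0.018 to 0.097 | 42% |
| 30 | 0.08 | 0.033 to 0.138 | 10% (gain significance) |
| 35 | 0.05 | 0.020 to 0.093 | 42% |

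**4. Long-run behaviour**, for equal arms and pairing unrelated to outcome (type I error from 40,000 simulated trials; power exact):

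| Per arm | Type I error, unpaired / paired | Power at 0.736 SD, unpaired / paired |
|---|---|---|
| 30 | 4.8% / 4.9% | 80.0% / 78.6% |
| 35 | 4.9% / 4.9% | 85.9% / 84.8% |

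At 30 per arm the two tests reach different conclusions in 1.6% of trials with no true difference and in 4.5% at the planned effect.

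**5. If the between-group test were dropped for within-arm tests.** Suppose both arms truly change by the same amount and each within-arm test has power w. The chance of significance in the intervention arm but not in the control arm is w(1 − w):

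- w = 0.3: 0.3 × 0.7 = 21%
- w = 0.5: 0.5 × 0.5 = 25%, the maximum
- w = 0.8: 0.8 × 0.2 = 16%

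Both arms receive new dentures, so a change in both is plausible.

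**The case against.** The strongest reply is that this is a drafting slip. One sentence covers two comparisons with one test name, and the word paired fits the second of them. The null hypothesis and the per-group sample sizes both point to an independent-groups contrast, and a competent analyst would probably run an unpaired test. That may well be the intention. But the sentence attaches the test to both comparisons, it appears twice, and on the charitable reading the article states no test at all for the randomised contrast. The text still has to be corrected.

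A second reply is that the allocation section also speaks of assignment in alternation, which might seem to create pairs of neighbouring enrolments. The same section specifies blocks of 10, and no pairing factor is described there or carried into the analysis.

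Several stronger readings are tempting, and the documents do not support them.

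- *The trial cannot give a valid answer, or its error rate is inflated.* With equal arms and pairing unrelated to outcome, type I error is held and the estimate does not change. Error rises sharply (to about 67% in simulation) only if both arms are sorted by outcome before pairing, which nothing in the article suggests.
- *Unpaired participants would be dropped.* The plan analyses by initial assignment and multiply imputes missing outcomes. Full enrolment of 70 is 70/10 = 7 complete blocks, so 35 against 35. Cases would be lost only if arm sizes differed, for example if enrolment stopped within a block.
- *A 25% false-positive rate.* That figure assumes that the between-group comparison listed in the plan is abandoned for within-arm significance, and that each arm has exactly 50% power. It is a conditional warning and does not describe the stated plan.

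It is also fair to say that an unpaired p of 0.05 is where any perturbation changes conclusions most, which is why the table also shows 0.03 and 0.08.

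**Conclusion.** The concern stands as a mis-specified primary test. The article names a paired t test for a contrast between independent, unmatched arms, so the pairs are undefined and the p-value is not reproducible. For results near the threshold the conclusion can turn on row order: about 17% of pairings lose significance at an unpaired p of 0.03, and about 10% gain it at 0.08, with 30 per arm. On average the cost is small, about 1.4 percentage points of power (80.0 − 78.6) with type I error near 5%.

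These figures assume normal data, equal arms and, for the error rate and power, pairing unrelated to outcome. The design, the data and the sample size are unaffected. The correction should nevertheless be made before results are known, because no other test of the primary hypothesis is stated.

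**What to change.** In the Statistical analysis section and in the abstract, separate the two comparisons.

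- Between groups, at 3 and at 6 months: an independent-groups method. The minimum is an unpaired (Welch) t test on change from baseline. ANCOVA of follow-up intake on group and baseline intake is preferable, since baseline intake is already collected. Report the difference with a 95% CI, pooled over the imputed data sets.
- Within groups: keep the paired t test, labelled descriptive, and state that it is not used to judge the effect of the advice.

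Replacing the test name for the between-group contrast is enough to cure the defect; the choice of ANCOVA is an improvement beyond that. The cost is one sentence in each of two places. No new data, participants or change of sample size are needed, and the article reports that recruitment is still under way, so the change can be dated before the results are known.

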## Discussion

This randomized controlled trial is designed to demonstrate the effect of simultaneous simple dietary advice and provision of new complete dentures in combination on dietary intake in edentulous individuals who request new dentures. It is hypothesized that a combination of provision of new complete dentures and simple dietary advice would improve nutrient intake among edentulous individuals.

Whereas in previous clinical research, nutritional intervention consisted of one-to-one counseling sessions with a nutritionist [1], the nutritional intervention in the present study consists of dentists giving participants a pamphlet along with a standardized detailed explanation of its contents. In a cohort study designed to determine if a combination of denture fixative use and dietary simple advice in the form of printed government-issued pamphlets would improve participants’ diets, fruit and vegetable intake was reported to improve over a 30-day period [3]. The researchers expected that this intervention would have a long-term effect on the basis that once a dietary choice is made, it is likely to continue.

Both participants and clinicians are blinded in this study so that neither will be aware of the allocated intervention. Nevertheless, the two outcome assessors (HS and NA) of the three outcome assessors (AJ, HS, and NA) will implement the randomization and allocation. These two outcome assessors also deliver advice, although they will not give complete denture treatments. Because these two outcome assessors are also delivering advice, neither outcome assessors nor those who deliver advice are blinded, which may cause bias. However, the bias against delivering advice has a smaller influence on the results of the research than the bias against giving treatments. Moreover, the outcomes assessed in this research consist of patient-reported outcomes and objective outcomes. Thus, only a small number of outcome assessors’ subjective outcomes are included, which leads to less possibility of observation bias.

An exclusion criterion for fruit and vegetable intakes at baseline is not set. Thus, participants whose fruit and vegetable intakes at baseline are already high might be included. However, it is reported that the mean consumption of vegetables in Japanese edentulous patients is lower than the Japanese government recommended vegetable intake of 350 g/d [38].

The effect of simple dietary advice alone in the absence of provision of complete dentures will not be investigated in this study. The previous study, aimed at complete denture wearers or implant overdenture wearers who did not need new dentures, showed that provision of tailored dietary counseling alone improves dietary intake in wearers of both types of dentures. In contrast, individuals who request new complete dentures are to be recruited in the present study. It would be unethical to withhold replacement of new dentures until completion of the study to investigate the effect of simple dietary advice alone in the absence of complete denture treatment. Therefore, the effect of simple dietary advice alone in the absence of provision of complete dentures will not be investigated in this study.

There is no opportunity for patients assigned to the control group to receive dietary advice; however, on completion of the study, the control group will receive the same dietary advice as the intervention group.

Simple dietary advice that can be implemented by a dentist is more practical in daily clinical practice than tailored dietary counseling, which requires the additional services of a nutritionist and a further appointment. The findings of this study will provide both patients and dentists with beneficial information with regard to improving dietary intake in edentulous individuals who request new complete dentures.

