## Abstract

**Background:**

Individuals who are edentulous have a lower intake of fruit, vegetables, fiber, and protein compared with their dentate counterparts because tooth loss is accompanied by a decrease in ability to chew. Whether or not a combination of prosthetic rehabilitation and simple dietary advice produces improvement in dietary intake among edentulous persons is unclear. We aim to investigate the effect of a simultaneous combination of simple dietary advice delivered by dentists and provision of new complete dentures on dietary intake in edentulous individuals who request new dentures.

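### The aim is worded as the effect of new dentures plus dietary advice in combination, but both arms receive new dentures, so the trial can identify only the added effect of dietary advice

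*Protocol article*

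**What the plan says.** Three places in the protocol article state the objective as the effect of the combination:

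- Abstract, Background: "We aim to investigate the effect of a simultaneous combination of simple dietary advice delivered by dentists and provision of new complete dentures".
- Methods/design, opening paragraph: the trial is "investigating the effect of a combination of simple dietary advice and provision of new complete dentures on dietary intake in elderly edentulous individuals".
- Discussion, first paragraph: the trial is "designed to demonstrate the effect of simultaneous simple dietary advice and provision of new complete dentures in combination on dietary intake", followed by "It is hypothesized that a combination of provision of new complete dentures and simple dietary advice would improve nutrient intake among edentulous individuals". No comparator is named.

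The end of the Background section puts it differently. The null hypothesis there is "no difference in dietary intake between edentulous individuals provided with simple dietary advice and new complete dentures" and "edentulous individuals provided with new dentures alone".

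On the design, Methods/design states that "All participants receive complete denture treatments". Under Interventions, the dietary group gets 20 minutes of dietary advice and the control group 20 minutes of denture-care advice, each with a pamphlet. The Statistical analysis section plans between-group comparisons at 3 and 6 months and adds that "within-group changes are to be compared using the paired *t* test". It sets 0.05 for each test and does not rank the two kinds of comparison.

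The Discussion acknowledges that dietary advice without new dentures is not studied, and gives an ethical reason. It does not say that the combination against no new dentures is equally out of reach.

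**The concern.** The article carries two questions. One is whether new dentures plus advice improve intake. The other is whether advice improves intake in people who are getting new dentures anyway. The first needs a comparison without new dentures, and no arm provides one. Only the second is randomised.

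The planned analysis closest to the first question is the before/after test in the intervention arm. That change mixes the advice with the new dentures, adaptation, season, repeated questionnaires and regression to the mean. Regression to the mean is plausible because people enter when a dental problem leads them to ask for dentures. Season is plausible because the diet questionnaire covers only the previous month and is repeated at 3 and 6 months.

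At stake is the reading of the results. A significant improvement within the intervention arm could be taken as support for the Discussion's hypothesis even if the arms do not differ. That would be an uncontrolled conclusion drawn from a randomised trial.

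**Working it through.** **1. What each arm receives**

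| Component | Dietary group | Control group |
|---|---|---|
| New complete dentures | yes | yes |
| Dietary advice, 20 minutes and pamphlet | yes | no |
| Denture-care advice, 20 minutes and pamphlet | no | yes |

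The denture row cancels in the between-group difference. What remains is dietary advice versus denture-care advice, given new dentures. This is the Background null hypothesis, except that the control arm receives denture-care advice as well as dentures.

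**2. The plan's own sample size**

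Inputs from Sample size estimation: 29 per group for 125 g/day of fruit and vegetables, 30 per group for 15 g/day of protein, 80% power, two-sided 0.05, 15% loss, target 35 per group.

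- Inflating 30 as 30 × 1.15 = 34.5 gives 35, the stated figure. Dividing, 30 / 0.85 = 35.3, gives 36. The two differ by one patient per group.
- No SD is stated, so 29 and 30 can only be solved backwards. With SD = d / [(1.960 + 0.842) × √(2/n)], the results are 125 / 0.736 ≈ 170 g and 15 / 0.723 ≈ 20.7 g.

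The figures are given per group for a difference, which reads as a two-group contrast. They fit the Background hypothesis, and nothing in them changes if the aim is reworded.

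**3. What a within-arm test shows when advice does nothing (illustration)**

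Assume no advice effect and a mean change of c SD (SD of the change) common to both arms. The documents give no value for c, so a range is shown. The probability that one arm's paired t test is significant is pw = P(|T| > t critical), where T is noncentral t with n − 1 degrees of freedom and noncentrality c√n. The arms are independent, so the probability that the intervention arm is significant and the control arm is not is pw(1 − pw).

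| c | n = 30: pw | pw(1 − pw) | n = 35: pw | pw(1 − pw) |
|---|---|---|---|---|
| 0 | 0.050 | 0.048 | 0.050 | 0.048 |
| 0.25 | 0.263 | 0.194 | 0.301 | 0.210 |
| 0.50 | 0.754 | 0.185 | 0.820 | 0.148 |
| 0.73 | 0.971 | 0.028 | 0.987 | 0.013 |

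The product cannot exceed 0.5 × 0.5 = 0.25. These are two-sided probabilities, so at c = 0 about half of the significant results would be in the direction of improvement. A valid two-sided between-group test at 0.05 favours the intervention 2.5% of the time whatever c is, because the common shift cancels.

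**The case against.** The strongest reply is that the operative hypothesis is already right. The Background gives the only null hypothesis stated for testing, and it is the add-on contrast. The sample size follows it, and the Statistical analysis section lists the between-group comparison first. Read in context, the word combination can describe the package given to the intervention arm. The practical conclusions in the Abstract and the Discussion concern simple advice against tailored counselling, not dentures against none. Withholding new dentures is called unethical, so the missing arm is not an oversight. Within-group tests beside a randomised comparison are not an error in themselves, and their ranking is commonly left to a full protocol or SAP that is not shown.

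Most of this stands. A reader might infer that the primary hypothesis test is mis-specified; the Background and the sample size section contradict that. A reader might also infer that a within-arm p < 0.05 would count as confirming the hypothesis. The article never says so: it does not tie the within-group tests to the combination or make them a success criterion.

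The reply does not remove the mismatch itself. The Discussion says that the trial is designed to demonstrate the effect of the combination, and the design cannot do so. The acknowledged limitation covers only advice without dentures. The lack of a stated priority would matter little alone; beside a hypothesis with no comparator, it leaves room for the wrong reading.

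**Conclusion.** The concern holds as an inconsistency of aim and hypothesis, with a risk of over-interpretation. The Abstract, Methods/design and Discussion claim an effect that the design cannot identify; the Background states the one that it can. The point about identification rests on the documents alone and needs no numerical assumption.

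Its numerical size cannot be fixed for this trial. With no advice effect, a significant change within the intervention arm has a probability of 5% with no common shift and 97% to 99% at 0.73 SD. It is tempting to quote a 25% false-positive rate for the pattern in which the intervention arm is significant and the control arm is not. That is only the peak of pw(1 − pw). The values in the table run from about 1% to 21%, they depend on a shift that the documents do not give, and the protocol does not adopt that decision rule. The 25% should not be cited as this trial's error rate.

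**What to change.** - Reword the aim and hypothesis in the Abstract, in the opening of Methods/design and in the first paragraph of the Discussion to match the Background: the effect on intake of adding simple dietary advice to new complete dentures, compared with new dentures and denture-care advice.
- State in the Statistical analysis section that conclusions about effect rest on the between-group estimate.
- Report within-group changes descriptively, as means with 95% confidence intervals and no significance tests.
- Extend the limitation in the Discussion to say that the effect of the combination against no new dentures is also not estimated.

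The cost is wording and a narrower claim. Arms, assessments and sample size stay as they are. The article reports that the trial is still recruiting, so the change can be made before analysis.

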### Interventions

All patients receive complete denture treatments. The technique used to create a complete denture involves primary and secondary impressions, recording of jaw relationships using occlusal rims, one or two trial insertions, and delivery of the new complete dentures. After delivery, adjustments to the dentures are made until both participant and clinician deem that no further adjustment is necessary. The new complete dentures are made by three dentists with 10–14 years of clinical experience (YK, MK, and MI). They will give complete denture treatments, but will neither deliver dietary advice or advice on care and maintenance of dentures nor assess outcomes. Participants will be randomly assigned to the three dentists.

Participants in the dietary intervention group receive 20 minutes of coordinated dietary advice in the form of an explanation of a pamphlet prepared with reference to the geriatric version of the Japanese Food Guide Spinning Top published by the Japanese Ministry of Agriculture, Forestry and Fisheries. The pamphlet is then given to the participant. If a participant does not prepare his or her own meals, the person who does the cooking receives the dietary advice as well.

Participants in the control group receive 20 minutes of coordinated advice for care and maintenance of dentures in the form of an explanation of a pamphlet prepared with reference to the guidelines published by the American Collage of Prosthodontics [23], after which the pamphlet is provided to the participant. The advice on diet and care and maintenance of dentures is provided by the two outcome assessors (HS and NA). The two-time deliveries of advice in the dietary intervention and control groups are designed to fit with dental appointments for try-insertion and delivery of new dentures.

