##### Assessment of antioxidant capacity

Antioxidant capacity will be assessed at baseline and at 3 months following intervention. The antioxidant potential is determined using a blood sample, and 8-hydroxy-2′-deoxyguanosine, a marker of oxidative stress, is measured in a urine sample. These markers are sensitive to changes in dietary intake of fresh fruit and vegetables. A 5-mL blood sample from each participant is collected into a K2EDTA vacutainer, from which plasma is separated and stored at −73 °C prior to analysis. All participants are required to have fasted for more than 8 hours prior to sampling, and all blood samples are taken at noon. Participants are also required to provide a 3-mL sample of morning urine.

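### The trial is called double-blind and its participants are said to be unaware of their allocation, but they know which advice they received and they self-report the primary outcomes

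*Protocol article*

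**What the plan says.** The Abstract and the opening of Methods/design both use the double-blind label; the latter reads "This double-blind, parallel, randomized controlled trial is investigating the effect". The section Randomization and allocation specifies who is meant: "Participants and clinicians will be blinded to the group allocation of each participant". The Discussion repeats the claim in its strongest form: "Both participants and clinicians are blinded in this study so that neither will be aware of the allocated intervention".

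The Interventions section describes what each arm receives. For the dietary arm: "Participants in the dietary intervention group receive 20 minutes of coordinated dietary advice in the form of an explanation of a pamphlet". For the control arm: "Participants in the control group receive 20 minutes of coordinated advice for care and maintenance of dentures", also by way of a pamphlet. In both arms the participant keeps the pamphlet, and advice is given at two dental visits (try-in and delivery). In the dietary arm, anyone else who cooks for the participant is advised too.

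Directly after the statement on participant blinding, Randomization and allocation adds: "The participants will be given repeated instructions not to reveal their group allocation to clinicians".

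Under Primary outcome measures, fruit, vegetable and protein intake are taken from a self-administered diet history questionnaire. The Discussion admits that outcome assessors and advice-givers are unblinded and that bias may follow. It then plays this down because the outcomes are either patient-reported or objective, so that few depend on an assessor's judgement.

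**The concern.** A participant who has twice been taken through a food-guide pamphlet, or twice through a denture-care pamphlet, knows which was received. The participant blinding that the protocol states is therefore not a property of the design.

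This matters because of who measures the primary outcomes. Blinding of the denture dentists guards against unequal denture treatment between arms. It does nothing about how participants fill in a diet questionnaire. Someone advised to change diet may report a better diet at 3 or 6 months without eating differently by that amount. If the double-blind label stands, a difference in self-reported intake would be presented with a protection that it does not have.

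**Working it through.** **Step 1. The text, side by side.**

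| Group | What the protocol claims | What its procedures imply |
|---|---|---|
| Participants | Blinded, unaware of allocation (Randomization and allocation; Discussion) | Openly different advice with a pamphlet to keep (Interventions); told not to reveal their group (Randomization and allocation). Not blinded. |
| Denture-making dentists | Blinded | Give no advice and assess no outcomes (Interventions). Blinding is feasible, provided that participants stay silent. |
| Advice-givers | Not blinded (Discussion) | Agrees. |
| Outcome assessors | Not blinded (Discussion) | Agrees; two of the three also deliver the advice. |

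The contradiction is confined to the first row. An instruction not to reveal one's allocation has meaning only for someone who knows it.

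**Step 2. Link to the primary outcomes.** All primary outcomes come from a self-administered questionnaire. The Discussion's reassurance deals with bias from assessors' judgement. It does not consider bias from the participant, who here is the observer.

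**Step 3. Illustration of size.** No figure in the protocol is in dispute here.

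Inputs from Sample size estimation: 29 per group, 80% power, difference 125 g/day, two-sided 0.05, and 15% loss from 35 per group, leaving 35 × 0.85 = 29.75 per arm. No SD is given, so the 29 cannot be checked independently; the SD has to be solved back from it.

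- Implied SD: the value at which a two-sample t test with n = 29 per group has 80% power for 125 g/day. By the noncentral t this is 167 g/day (170 by the normal approximation).
- Standard error of the difference: 167 × √(2/29) ≈ 43.9 g/day.
- With no true effect and over-reporting of b g/day in the dietary arm, the test statistic is noncentral t with 2 × 29 − 2 = 56 degrees of freedom and noncentrality b / 43.9. The false-positive rate is the probability that it exceeds the two-sided 5% critical value in absolute size.

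| Assumed over-reporting b (g/day) | Share of 125 g | Noncentrality | False-positive rate |
|---|---|---|---|
| 0 | 0% | 0 | 5.0% |
| 12.5 | 10% | 0.28 | 5.9% |
| 25 | 20% | 0.57 | 8.7% |
| 37.5 | 30% | 0.85 | 13.4% |
| 62.5 | 50% | 1.42 | 28.8% |

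For protein (30 per group, 15 g/day, implied SD about 20.4 g/day) the same shares are 1.5, 3, 4.5 and 7.5 g/day and give the same rates. The values of b are assumptions; the documents supply none.

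**The case against.** The strongest defence is that the control arm is matched for session length and pamphlet format. Participants may therefore not know which advice is the experimental one, and blinded may have been meant in that sense. This is possible: the consent material is not available here, so masking to the hypothesis cannot be ruled out. But it is not what the article says. The article claims unawareness of the allocated intervention, and that does not hold whatever participants know about the hypothesis.

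Several stronger readings are tempting and should not be drawn:

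- *That no blinding exists.* The denture dentists' separation from advice and assessment makes their blinding feasible, and nothing in the document contradicts it.
- *That the protocol hides unblinded staff.* It discloses that assessors and advice-givers are unblinded. Only the participants' position is misdescribed.
- *That the Discussion claims patient reporting protects against participant bias.* Its argument concerns assessors' subjective judgement. The fault is that participant bias is left out.
- *That participants answer fresh from the advice.* Outcomes are taken 3 and 6 months after the intervention, and the questionnaire covers the previous month. Differential reporting is still possible at that distance, but its size is unknown.
- *That a particular inflated error rate applies.* At small assumed biases the rate barely leaves 5%; only near half the design difference does it approach 29%.

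**Conclusion.** The point holds for participant blinding. The double-blind label and the statements that participants are blinded are contradicted by the protocol's own interventions and by its instruction to participants. The primary outcomes are self-reported by people who know what advice they had, so they are open to differential reporting, and the Discussion does not acknowledge this.

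This conclusion rests on the text and needs no assumed bias. The range of about 6% to 29% false positives is illustrative only. It depends on assumed over-reporting of 12.5 to 62.5 g/day, on an SD solved back from the sample size statement, and on about 30 participants per arm. The documents do not show that such bias will occur. Nor does the finding make the design unusable: it limits what a between-group difference in reported intake can be said to show.

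**What to change.** - In the Abstract, Methods/design, Randomization and allocation, and Discussion, replace the double-blind label and the participant-blinding statements with: *treating dentists blinded; participants, advice-givers and outcome assessors not blinded*. Add that participants are unaware of the study hypothesis only if that is true.
- State in the Discussion that between-group differences in the primary outcomes are differences in reported intake and are open to reporting bias.
- Report the antioxidant markers, which are already collected, as supportive evidence. Of these the protocol says: "These markers are sensitive to changes in dietary intake of fresh fruit and vegetables". They are measured only at baseline and 3 months, so they can support fruit and vegetable intake at 3 months, but not protein and not the 6-month results. Do not add a rule that a null marker result cancels the primary finding: the protocol gives no threshold or power for the markers, so such a rule would create an inferential problem of its own.
- If the possible size of reporting bias is illustrated, label it as assumed and give a range.

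The cost is wording only: no new measurement, and no change in how participants are treated or informed. The downside is a less favourable design label.
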